### Data collection

2.17

Data for this study will be collected using a fully digital, longitudinal approach aligned with the hybrid trial design, integrating repeated measures, online platform derived engagement data, and anonymized facility based verification (52, 57).

Data collection procedures are prespecified in the study Data Management Plan (DMP; DMPTool Registry No.10.48321D1D8C7728A), ensuring transparency and reproducibility (30). Data will be collected at baseline (Week 0) and during follow up assessments at Weeks 2, 6, 10, and 12 using standardized electronic data collection instruments.

Baseline data will include demographic characteristics, socioeconomic characteristics, HIV testing history, HIV related knowledge, digital media use, and other variables relevant to the study objectives.

Follow up assessments will capture intervention exposure, participant engagement, HIV testing behavior since the previous assessment, linkage to care, adverse events, and protocol deviations.

All questionnaires will be completed electronically through secure online platforms using standardized instruments across all study arms.

Intervention engagement will be monitored using WhatsApp platform metrics, including message delivery, read status, participant responses, and interaction frequency to assess intervention fidelity.

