#### Primary outcome

2.15.1

The primary outcome is HIV testing uptake, defined as completion of at least one HIV test during the 12 week follow up period after randomization, irrespective of HIV test result.

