#### Survey instrument

2.17.1

The primary outcome will be measured using standardized electronic questionnaires administered at each follow up assessment.

Participants will be asked:

*“At any time during the past 4 weeks, have you had an HIV test?”*

Responses will be recorded as Yes or No.

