#### Data collection time points

2.17.2

Data will be collected at five predefined study time points:

Baseline (Week 0; preintervention)Week 2 (early exposure)Week 6 (midline)Week 10 (late exposure)Week 12 (endline)

This repeated measures structure enables longitudinal analysis across study arms (23).

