#### Data analysis plan

2.18.3

Data analysis will follow an intention-to-treat (ITT) approach (36).

Analytical methods will include:

Descriptive statisticsChi-square tests (55)McNemar’s and Cochran’s *Q* tests (22, 58)Logistic regression (37)Thematic qualitative analysisCost-effectiveness analysis (38)

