#### Primary analysis

2.19.1

The primary outcome will be analyzed using generalized linear mixed effects models (GLMMs) with a link to compare HIV testing uptake between study arms over time while accounting for within participant correlation.

Fixed effects will include:

Study armFollow up timeArm × time interaction

Random intercepts will account for repeated observations within participants.

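### The follow-up windows are unequal, so comparing raw per-visit testing proportions over time would show a false rise after Week 2, and under one of the two stated recall periods a false fall at Week 12

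*Protocol article*

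**What the plan says.** Section 2.17 (Data collection) schedules "follow up assessments at Weeks 2, 6, 10, and 12" and says that these capture "HIV testing behavior since the previous assessment". Section 2.17.1 (Survey instrument) prints the question: "At any time during the past 4 weeks, have you had an HIV test". It adds: "The primary outcome will be measured using standardized electronic questionnaires administered at each follow up assessment". The two sections therefore give different recall periods for the same visits.

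Section 2.15.2 lists repeated testing over time as a secondary outcome. Section 2.17.2 labels the four follow-ups as early exposure, midline, late exposure and endline, and states: "This repeated measures structure enables longitudinal analysis across study arms". The listed methods include "McNemar’s and Cochran’s" Q tests (section 2.18.3, again in 2.19.2). The mixed model in section 2.19.1, with arm, time and their interaction, is meant to "compare HIV testing uptake between study arms over time while accounting for within participant correlation".

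The primary outcome is cumulative: "completion of at least one HIV test during the 12 week follow up period after randomization" (section 2.15.1). Under section 2.16 a test counts only once the facility has confirmed it.

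**The concern.** A proportion tested at a visit depends on how many weeks the answer covers. If one visit covers 2 weeks and the next covers 4, the second proportion is nearly twice the first even when behaviour has not changed. Cochran's Q and McNemar's test compare raw proportions within the same men and cannot take a denominator of weeks observed. The time effect of a mixed model without an offset carries the same artefact.

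At stake is the description of the time course. A trial in which testing ran at a steady rate could report that uptake climbed by midline and, under one of the two recall definitions, waned at endline. Such a finding could influence views on how long the messaging should run.

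**Working it through.** The article gives no per-visit proportion, so there is no stated figure to reproduce.

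**Inputs.** Visits at Weeks 0, 2, 6, 10 and 12 (section 2.17). Uptake of 20% and 40%, and 156 men per arm (section 2.8). Assumptions: these uptakes are 12-week values, the testing rate is constant, and tests in separate periods are independent.

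**Window lengths.**

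| Visit | Since previous assessment | Past 4 weeks, as asked | Past 4 weeks, post-randomization only |
|---|---|---|---|
| Week 2 | 0 to 2 (2 wk) | −2 to 2 (4 wk) | 0 to 2 (2 wk) |
| Week 6 | 2 to 6 (4 wk) | 2 to 6 (4 wk) | 2 to 6 (4 wk) |
| Week 10 | 6 to 10 (4 wk) | 6 to 10 (4 wk) | 6 to 10 (4 wk) |
| Week 12 | 10 to 12 (2 wk) | 8 to 12 (4 wk) | 8 to 12 (4 wk) |

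Under the 4-week question the Week 10 and Week 12 answers share weeks 8 to 10, so one test can be reported twice.

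**Expected proportions.** Weekly rate h = −ln(1 − P)/12; probability in a window of L weeks = 1 − exp(−hL).

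- P = 20%: h = 0.0186. Two weeks give 3.7% and four weeks 7.2%, a ratio of 1.96.
- P = 40%: h = 0.0426. Two weeks give 8.2% and four weeks 15.7%, a ratio of 1.92.

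The expected series with no true change are:

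- Since previous assessment: 3.7, 7.2, 7.2, 3.7% at P = 20%; 8.2, 15.7, 15.7, 8.2% at P = 40% (about 13, 24, 24 and 13 men of 156).
- Past 4 weeks, post-randomization only: 3.7, 7.2, 7.2, 7.2%; 8.2, 15.7, 15.7, 15.7%.
- Past 4 weeks as asked, if the same rate held before randomization and those tests counted: flat at 7.2% or 15.7%.

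**False rejection of no change.** Simulated at 0.05 with n = 156, mostly 4,000 runs per setting. Ranges show the spread between repeated simulations.

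| Windows | Cochran's Q, P = 20% | Cochran's Q, P = 40% | McNemar Week 10 v 12, P = 20% and 40% |
|---|---|---|---|
| 2, 4, 4, 2 | 31% to 33% | 67% to 69% | about 19% and 46% |
| 2, 4, 4, 4 (last two overlapping) | 25% to 26% | 51% to 54% | 2% to 3% |
| Past 4 weeks as asked | 4% to 6% | 4% to 6% | 2% to 3% |
| Four equal 3-week windows | about 5% | about 5% | not needed |

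McNemar's test of Week 2 v Week 6 rejects in about 21% and 46% whenever only post-randomization tests count.

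**Between-arm contrast at one visit, 20% v 40%.** The odds ratio in a 2-week window is (0.0816/0.9184)/(0.0365/0.9635) = 2.35. In a 4-week window it is (0.1566/0.8434)/(0.0717/0.9283) = 2.40. Window length hardly moves it.

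**Missed visits, under section 2.17's wording only.** Assume 20% of men miss each visit at random and the next answer covers the gap. At P = 20%, the Week 10 proportion becomes 0.80 × 7.2% + 0.16 × 13.8% (8 weeks) + 0.04 × 17.0% (10 weeks) = 8.6%, an inflation of about 20%. The Week 12 proportion is inflated by 41% to 45% across the two uptakes. At 5% missed, the figures are about 4% to 5% and 9% to 10%.

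**The case against.** The strongest reply is that the only instrument shown asks about a fixed 4 weeks, so the windows are equal, the series is flat and Cochran's Q holds its level. That is correct if tests before randomization count. The plan points the other way: the primary outcome is defined after randomization, and a test must be confirmed through a code issued at enrolment. With pre-randomization tests removed, the Week 2 window is 2 weeks and the rise to Week 6 remains. The fall at Week 12 does not, and neither do the high McNemar rejection rates for Week 10 v Week 12.

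A reader might therefore infer a doubling followed by a halving whatever is measured. The documents do not support that, because the halving needs section 2.17's wording to prevail. A reader might also infer bias between arms from missed visits. That too needs section 2.17's wording, plus a miss rate that differs by arm, for which the documents give no basis.

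It is also fair to say that no section assigns Cochran's Q or McNemar's test to the repeat-testing outcome, that the mixed model is given for the primary outcome, and that the coding of time may be settled in the SAP, which is not shown. This stands as a limit, since the link between test and outcome is inferred. Categorical time would absorb a window effect common to all arms when arms are contrasted. It would not stop the time effect itself from being read as behaviour change, and it does nothing for the two within-person tests.

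**Conclusion.** The point holds in a limited form. The two recall definitions conflict. Under either one, once only post-randomization tests count, raw per-visit proportions show a near-doubling from Week 2 to Week 6 (ratio 1.92 to 1.96) with no change in behaviour. A false halving at Week 12 arises only under section 2.17's wording. For 12-week uptake of 20% to 40% and 156 men per arm, the false rejection rate of Cochran's Q is about 32% to 69% under section 2.17 and about 25% to 54% under section 2.17.1 with pre-randomization tests removed.

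These sizes rest on a constant rate, independence between periods, reading the planning uptakes as 12-week values, and use of the listed tests for this outcome. The effect is confined to within-arm time trends in a secondary outcome. The arm contrast at a visit and the cumulative 12-week primary outcome are essentially unaffected. It should be corrected before analysis, but it does not threaten the trial's main comparison.

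**What to change.** 1. Reconcile the recall periods in sections 2.17 and 2.17.1, and state whether tests before randomization are excluded at Week 2 and how the Week 10 and Week 12 overlap is handled.
2. For the repeat-testing outcome, place facility-verified tests by date into equal windows from randomization (weeks 0 to 4, 4 to 8 and 8 to 12) and compare those. Alternatively, keep the visit intervals and model verified tests per person-week with log(weeks covered) as an offset, using a Poisson mixed model or a binary one with a complementary log-log link. Report trends as tests per 100 person-weeks.
3. State that Cochran's Q and McNemar's test will not be applied across windows of unequal length.

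The cost is protocol and SAP wording and a few lines of code. Facility test dates, or for the offset model the dates of consecutive assessments, must be available and used. Rates per person-week are a little less familiar to readers than simple proportions.

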#### Survey instrument

2.17.1

The primary outcome will be measured using standardized electronic questionnaires administered at each follow up assessment.

Participants will be asked:

*“At any time during the past 4 weeks, have you had an HIV test?”*

Responses will be recorded as Yes or No.

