### Outcome verification

2.16

PEach participant will receive a Unique Referral Identification Code (URIC) for enrolment. The URIC is a unique study generated identifier that anonymously links participant self reports with partner health facility records without recording personal identifiers in the research database.

Participants will present their URIC whenever attending the partner HTS facility for HIV testing. Facility staff will record the URIC together with confirmation that HIV testing was completed.

HIV testing uptake will be verified using three complementary data sources:

Participant self report;Anonymized partner facility HIV testing records; andURIC redemption.

A participant will be classified as having completed HIV testing only after facility verification confirms test completion. This hybrid verification model minimizes outcome misclassification, reduces recall bias, strengthens internal validity, and preserves participant confidentiality (29). This approach improves validity by reducing reliance on self report alone and is consistent with best practices in behavioral intervention trials (29).

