#### Missing data

2.19.3

Missing outcome data will be examined and, where appropriate, addressed using multiple imputation. Sensitivity analyses will assess the robustness of study findings (45).

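### The fixed four-week recall question does not fit surveys at Weeks 2, 6, 10 and 12, and the survey section conflicts with the facility-verified definition of the primary outcome

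*Protocol article*

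**What the plan says.** Section 2.17.1 (Survey instrument) fixes one yes/no question, "At any time during the past 4 weeks, have you had an HIV test", and gives it a role: "The primary outcome will be measured using standardized electronic questionnaires administered at each follow up assessment".

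Section 2.17 (Data collection) sets the schedule: "Data will be collected at baseline (Week 0) and during follow up assessments at Weeks 2, 6, 10, and 12". It also says that follow-up surveys capture "HIV testing behavior since the previous assessment", which is a different recall period.

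Section 2.15.1 defines the primary outcome as "completion of at least one HIV test during the 12 week follow up period after randomization, irrespective of HIV test result". Section 2.9 places allocation after consent and the baseline assessment.

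Section 2.16 (Outcome verification) states: "A participant will be classified as having completed HIV testing only after facility verification confirms test completion". It lists self-report as one of three sources, beside facility records and redemption of the referral code (URIC).

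Section 2.19.1 fits a generalised linear mixed model (GLMM) to repeated observations, with arm, time and their interaction. It does not say whether the response at each time is the survey answer or a verified test. Repeated testing over time is a secondary outcome (2.15.2), and Cochran's Q and McNemar's tests are planned (2.19.2).

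**The concern.** A fixed four-week look-back covers follow-up exactly once only if the surveys are four weeks apart. Here the gaps are 2, 4, 4 and 2 weeks, so the question overshoots at the first and last surveys. At Week 2 it takes in tests done before randomisation, which the outcome definition excludes and which no arm could have caused. At Week 12 a single test in weeks 8 to 10 can be reported a second time. A man who misses Week 6 has no later chance to report a test from weeks 2 to 6, because the Week 10 question reaches back only to Week 6.

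The second problem is the source. One section has the questionnaire measure the primary outcome; another accepts a test only once the facility confirms it. The primary model needs a response at each visit, and the survey question is the only visit-level outcome item that the article describes. An analyst could reasonably use either source. The answers are undated, so pre-randomisation and duplicate reports cannot be separated afterwards.

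**Working it through.** The plan states no figure on this point, so there is none to reproduce. The windows follow from the schedule. The sizes are an illustration on stated assumptions.

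**1. Windows.** Randomisation is taken as Week 0, since it follows baseline.

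| Survey | Four-week look-back | Since previous assessment | Agree? |
|---|---|---|---|
| Week 2 | −2 to 2 | 0 to 2 | No: 2 of 4 weeks precede randomisation |
| Week 6 | 2 to 6 | 2 to 6 | Yes |
| Week 10 | 6 to 10 | 6 to 10 | Yes |
| Week 12 | 8 to 12 | 10 to 12 | No: weeks 8 to 10 already asked |

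The four-week question asks about 4 × 4 = 16 weeks. Of these, 2 precede randomisation and 2 are repeats, leaving 16 − 2 − 2 = 12. The other rule covers weeks 0 to 12 exactly once.

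**2. Assumptions for size.** Twelve-week uptake is 20% and 40%, as in the power calculation of section 2.8. The testing hazard is constant within each arm. The control hazard applies to both arms before randomisation. Survey answers alone form the response.

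**3. Week 2 odds ratio.** Uptake over two weeks is 1 − (1 − p)^(2/12).
- 20% arm: 1 − 0.8^(1/6) = 0.0365. 40% arm: 1 − 0.6^(1/6) = 0.0816.
- True odds ratio: (0.0816/0.9184) / (0.0365/0.9635) = 2.35.
- Recorded, 20% arm: 1 − 0.9635 × 0.9635 = 0.0717. Recorded, 40% arm: 1 − 0.9184 × 0.9635 = 0.1151.
- Recorded odds ratio: (0.1151/0.8849) / (0.0717/0.9283) = 1.69.
- Share of Yes answers due only to pre-randomisation tests: (0.0717 − 0.0365)/0.0717 = 49% in the 20% arm, and (0.1151 − 0.0816)/0.1151 = 29% in the 40% arm.
- With 20% v 30% instead, the odds ratio falls from 1.62 to 1.31.

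**4. False repeats, if Yes answers are counted.** Tests are Poisson with mean m = −ln(1 − p). True repeats are P(≥2) = p − m(1 − p). A single test falls in weeks 8 to 10 with probability m(1 − p) × 2/12.
- 20% arm: m = 0.223. True repeats 0.20 − 0.1785 = 2.1%; false repeats 0.1785/6 = 3.0 points.
- 40% arm: m = 0.511. True repeats 0.40 − 0.3065 = 9.4% (0.0935); false repeats 0.3065/6 = 5.1 points.

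**5. Any test in 12 weeks.**
- 20% arm: 1 − 0.8 × 0.9635 = 22.9%. 40% arm: 1 − 0.6 × 0.9635 = 42.2%.
- Contrast: 42.2 − 22.9 = 19.3 points against 20.0. Power at 156 per arm goes from 97.4% to 95.6%.
- In general the contrast is 20 × (1 − b)^(1/6), where b is 12-week background uptake before randomisation. For b of 5%, 10%, 20% and 30% it is 19.8, 19.7, 19.3 and 18.8 points.

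**The case against.** The strongest reply is that the article largely settles which source governs. Section 2.16 is explicit, the abstract calls the outcome verified uptake, and the discussion repeats it. On that view section 2.17.1 is the outlier and describes only the self-report component. The URIC is issued for enrolment, so a test done before it would ordinarily have no redemption. Facility records also do not depend on whether a man completes a survey. Most of this stands, and it limits the harm. It does not remove the conflict in the text, and it does not say what the model analyses at each visit.

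A reader might infer four stronger things that the document does not support.

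- **That recorded primary uptake would be 22.9% rather than 20%.** This needs survey answers alone to classify the outcome, which section 2.16 rules out. Even then the contrast moves by only 0.7 points.
- **That double coverage corrupts the primary endpoint.** Asking twice about weeks 8 to 10 cannot change an outcome of at least one test.
- **That repeat testing would more than double.** In this illustration that holds only in the 20% arm (2.1% plus 3.0 points). In the 40% arm the rise is about 55% (5.1/9.35). Both assume that repeats are scored by counting Yes answers, which the article does not state.
- **That imputation would credit tests to men with no facility record.** Section 2.19.3 says only: "Missing outcome data will be examined and, where appropriate, addressed using multiple imputation". How men without a record are handled belongs to an analysis plan that is not shown.

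**Conclusion.** The concern holds as an internal inconsistency that should be fixed. The two recall periods disagree at two of the four follow-ups, the four-week question contradicts the post-randomisation definition at Week 2, and two sections give different sources for the primary outcome. These points rest on the text and the schedule alone.

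The size depends on how the data are used. If survey answers feed the visit-level model or the count of repeat tests, the distortion is material: a Week 2 odds ratio of about 1.69 instead of 2.35, and 3.0 to 5.1 points of false repeats. Those figures rest on assumed constant hazards and on the control hazard before randomisation. If only facility-verified tests count, the harm is largely confined to the self-report data and the analyses that use them. The 12-week contrast is little affected either way. Severity: should fix.

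**What to change.** 1. **Question (2.17.1).** Anchor it to the enrolment date at Week 2 and to the date of the last completed survey at later visits, and ask the date and place of any test. This removes the pre-randomisation time and the overlap, and it recovers tests from an interval whose survey was missed. Align section 2.17 with the same wording.
2. **Source (2.17.1).** Say that the questionnaire supplies the self-report component, and that the primary outcome is the verified test of section 2.16, dated after randomisation and within 12 weeks.
3. **Model (2.19.1).** State that the GLMM response uses that verified outcome.

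The fix need not declare that a man without a facility record counts as not tested. That is a choice of estimand, not of wording: section 2.10 names encouragement to the partner facility only for Arm 3, and the discussion concedes that tests elsewhere may be missed, so capture could differ by arm.

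The cost is revised questionnaire wording and a few protocol sentences. It should be done before follow-up surveys begin, because undated answers cannot be repaired later.

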#### Data collection time points

2.17.2

Data will be collected at five predefined study time points:

Baseline (Week 0; preintervention)Week 2 (early exposure)Week 6 (midline)Week 10 (late exposure)Week 12 (endline)

This repeated measures structure enables longitudinal analysis across study arms (23).

#### Baseline assessment

2.17.3

Baseline assessment will collect:

AgeEducationEmployment statusPrevious HIV testing historyHIV-related knowledgeDigital access and WhatsApp useBehavioral risk characteristics

#### Intervention engagement

2.17.4

Intervention engagement will be monitored using WhatsApp interaction metrics, including message delivery, read status, participant responses, and participation frequency. These indicators will be used to assess intervention fidelity (31).

#### Retention and attrition management

2.17.5

Retention strategies will include automated reminders, responsive participant communication, and continuous engagement via study channels (32).

Attrition will be monitored weekly. Where attrition exceeds predefined thresholds, additional participant follow-up strategies will be implemented.

### Data management

2.18

All data will be collected and stored electronically using secure systems, including encrypted, password protected platforms. WhatsApp identifiers will be replaced with unique study IDs, and only de-identified datasets will be used for analysis. Access to identifiable data will be restricted to authorized personnel. Daily encrypted backups will be maintained.

Data management procedures are specified in the study Data Management Plan (DMPTool Registry No. 10.48321D1D8C7728A).

Study data will be collected and stored electronically using encrypted password protected systems.

Participants will be identified only by unique study identification numbers. Personally identifiable information will be stored separately from research data. Outcome verification data obtained from partner health facilities will be linked using the URIC without recording participant names within the analytical dataset.

Access to identifiable information will be restricted to authorized study personnel. Encrypted backups will be performed regularly.

Data management procedures comply with international security standards [ISO/IEC 27001; (33)].

